### Data management

The study will be performed in accordance with the General Data Protection Regulations (GDPR). The study is reported to The Danish Data Protection Agency (journal no. 1–16-02–398-21), and in accordance with their rules, we report that the expected time for completion of the project and deletion, anonymization, or transfer to the National Archives is 4 October 2026. After data collection, a member of the research team will check data to identify and, where possible, resolve errors prior to analyses being conducted. Two members of the research team will independently prepare data prior to the main analysis. All computers and servers used to manage data and contact with participants will be password protected and housed in secure environments. The Central Denmark Region will provide secure IT systems for secure data management and processing. Register data is managed through IT infrastructure provided by Statistics Denmark. Survey data is collected using SurveyXact. The Central Denmark Region has data management agreements with both Statistics Denmark and SurveyXact. Access to the collected data will only be granted to the research team.

### Monitoring

The project is managed by Steno Diabetes Center Aarhus (SDCA) who will have access to the final dataset. A steering committee consists of the chief executive officer, chief clinician, researchers, [name], and an administrative staff member. On regular meetings, the steering committee will monitor the study procedures and ensure that the trial is being conducted according to the study protocol. The data management team will have clinical, research, and statistical expertise and will consist of the research team, a statistician, and post doc. No interim analyses or auditing are planned since the intervention has been successfully piloted with GPs, and the intervention is not expected to result in any potentially serious outcomes.

## Dissemination plan

Regardless of the magnitude or direction of effect, trial results will be presented at relevant national and international conferences and as published articles in peer-reviewed journals. The analysis is expected to be completed six months after each intervention period ends. The project is expected to result in a minimum of three articles reporting on, respectively, patient outcomes, general practice outcomes, and a qualitative article about the process evaluation. Publication of the study results will be based on the CONSORT extension for pragmatic randomized trials statement [25]. The authorships will follow the International committee of medical journal editors (ICMJE) guidelines. The study results will be disseminated to health care professionals and researchers at (inter)national conferences. The public will learn about the findings in newsletters and via social media. To reach health care policy audiences (e.g. government bodies and unions), plain language findings will be presented at policy maker- and service provider-run conferences.

## Discussion

The intervention relies on randomization of general practices, thereby not targeting a certain type of general practice. The randomization allows for generalizing findings and the qualitative evaluation provides points of learning to GPs across the five Danish regions. The project results also have broader perspectives as the intervention can be applied to other chronic diseases or conditions where dialogue between the hospital and GPs is needed to support the latter in caring for their patients. The results and intervention are also expected to be applicable to other countries with a health system similar to the Danish such as the English NHS. The generalizability is moreover fostered by performing a process evaluation to assess the fidelity of the intervention alongside identification of organizational factors (e.g., how service is delivered) [42].

Given the design of the study, five major limitations apply. First, patient outcomes rely on data retrieved from an IT-platform (Diabetes Overview), and the precision of the outcomes thus depends on the quality of and reporting to the underlying database. Overall, data in Danish registries have high accuracy [46, 47]. To ensure data quality, the first introductory virtual conference serves an important aim and that is getting the GPs to review their list of patients with diabetes (i.e., enter or remove patients) by ensuring that those on the list have the correct diagnostic codes. When patients are registered correctly, data are automatically shown in the Diabetes Overview. The data will be provided by the participating GPs, a task for which they are remunerated, thereby ensuring availability of data.

Second, getting GPs to participate in research projects in Denmark can be difficult because they operate as private for-profit firms, and patient demands means they often work on a tight schedule [30]. Recruitment of GPs during the COVID-19 pandemic is even more challenging [48]. Nevertheless, our recruitment strategy in six steps (e.g., reimbursement and phone calling) are expected to facilitate recruitment. Third, we risk that only GPs participate who are particularly interested in diabetes, thereby resulting in a biased sample. By comparing the sample with the population of GPs and general practices in Aarhus Municipality, we will analyse how similar the sample is to the population.

Fourth, GPs and endocrinologists cannot be blinded to their allocation status. To limit that the behaviour of the control group is influenced, baseline information will not be collected and they are not informed about the data we will collect at month 12. However, participants in the control group can on their own decide to improve the management of T2D by, for example, taking courses and thus move closer to the outcomes of the intervention group. The degree to which this is the case will be captured by asking about changes made during the past year. Fifth, common method bias [49] is considered a small potential risk in the study even though self-reported data (i.e., survey to GPs and practice staff) and administrative health data from the Diabetes Overview (i.e., screen shoots of the primary and secondary outcomes) are collected from the same data source. The risk is moreover considered small because the administrative health data is updated automatically, and the two types of data are collected at different points in time.

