#### Intervention arm

Table 1 provides a detailed description of the intervention according to the *Template for Intervention Description and Replication checklist and guide* (TIDieR) [34]. The intervention consists of four virtual conferences (45 min) between endocrinologists and an individual general practice that take place over a period of 12 months (month 2, 5, 8, and 11). Before having the first virtual conference, an introductory webinar (90 min in month 1) is held to learn GPs about how to use the electronic “Diabetes Overview” to identify and manage patients with T2D.

**Table 1 Tab1:** Intervention according to TIDieR (Template for Intervention Description and Replication)

Brief name	Virtual specialist conferences between general practitioners and endocrinologists about type 2 diabetes
Why	To support general practitioners (GP) in managing their patients living with type 2 diabetes (T2D). To optimize pharmacological treatment of patients with T2D
What	Virtual conferences between GPs and endocrinologists lasting approx. 45 min. The four conferences are thematic: (1) T2D and cardiovascular disease and heart failure, (2) T2D and cholesterol and lipids, (3) T2D and kidney disease and blood pressure, and (4) T2D and a free topic. The GP is asked to bring to each conference 2–3 patient cases related to the theme and 1–2 patient cases of their own choice. Each conference follows the same format: (1) check in (5 min), (2) presentation by endocrinologist on the conference theme with a focus on medication and treatment guidelines (10 min), (3) presentation by GP and joint dialogue about 2–3 patients related to the theme (20 min), (4) presentation by GP and joint dialogue about 1–2 patients unrelated to the theme (optional; 5 min), and (5) wrapping up and summary of learning points (5 min) Before the first virtual conference, an introductory webinar (90 min) is held to learn GPs about how to use the electronic “Diabetes Overview” to identify and manage patients with T2D All conferences and webinars are carried out according to a manual

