Who provided	Preparation and roles before and during virtual conferences: GP(s): - Chair of the meeting - Finds patient cases via “Diabetes Overview” - Presents patient cases General practice staff: - Participates in the dialogue Endocrinologists from Steno Diabetes Center Aarhus. Each general practice meets the same endocrinologist in all the conferences: - Presentation on the conference theme - Dialogue about and advises on patient cases
How	Virtual conferences between one endocrinologist and at least one GP from each general practice. MDs in training and practice staff from the general practice is encouraged to participate The virtual conference is integrated into the working plan of the endocrinologists GPs are responsible for planning their own clinical programme
Where	Virtual meeting platform. The endocrinologists will be sitting at Aarhus University hospital. The GPs will be sitting in their practice or at home
When and how much?	Each general practice will receive four conferences in 1 year each lasting approx. 45 min and one introductory webinar (90 min)
Tailoring	GPs decide themselves on which patient cases they want to bring to the conferences: 2–3 related to the theme and 1–2 patient cases of their own choice
Modifications	Modifications due to changing circumstances or on behalf of the participants will be noted throughout
How well	Adherence and fidelity in the outcome study is analysed, and the trial will study process outcomes

Each general practice is assigned to an endocrinologist who they meet at all four conferences. The four virtual conferences are thematic: [1] T2D and cardiovascular disease and heart failure, [2] T2D and lipids, [3] T2D and kidney disease and blood pressure, and [4] T2D and a free topic selected by the GP. The GP is asked to bring two–three patient cases to each conference who are related to the theme and one-two patient cases of their own choice. The GP chairs the meeting. Each virtual conference follows the same format: [1] check in (5 min); [2] short presentation by the endocrinologist on the conference theme with a focus on medication and treatment guidelines (10 min); (3) presentation by GP and joint dialogue about 2–3 patients related to the theme (20 min); (4) presentation by GP and joint dialogue about 1–2 patients unrelated to the theme (optional; 5 min); and (5) wrapping up and summary of learning points (5 min).

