#### Comparison arm

General practices allocated to the control group will continue to get access to the usual written or telephone support by an endocrinologist in hospitals. This requirement to provide diabetes support to GPs is part of a collective agreement between the Danish Regions and the Association of General Practitioners [35]. The control group will get the intervention after the primary intervention ends, that is, after month 12.

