#### Clinical outcomes

Clinical outcomes will be collected from an IT-platform (DEN: “Diabetes Overblik”. ENG: “Diabetes Overview”) used by Danish general practices, which contains anonymous and aggregated diabetes data about patients (Additional file 3 shows screenshots). As per the agreement to participate in the study, each general practice assigns a contact person who will e-mail the screenshot of the data to the project group. Each general practice is renumerated for performing this activity. Data will also be obtained from nationwide Danish registries: The Clinical Laboratory Information System Research Database (LABKA), The Danish National Prescription Registry (DNPR), The Danish National Health Service Register (NHSR), The Danish Civil Registration System (CRS), and The Danish National Patient Register (NPR). Register data will be linked to the unique provider number of each general practice.

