#### Difference between intervention and control group

The main analysis concerns the difference between the intervention and control group at month 12. Data from the Diabetes Overview and general practice survey are analysed using simple, multiple, and logistic regression analyses. Analysis is done according to the intention-to-treat principle to test if the groups differ in terms of outcome measures. The analysis of survey data will take into account cluster effects using the intra-cluster correlation coefficient. Using *t*-test and *Χ*^2^ tests, depending on the outcome measure, it will be determined if randomization has resulted in systematically different groups. Survey data are tested to determine if questions or indices of questions are internally consistent (Cronbach alpha). In the regression analyses, control variables at the individual (e.g., seniority) and practice level (e.g., form and size of practice) are tested to determine its influence on survey outcomes.

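### The diabetes list review falls in the intervention arm only before month 12, and the outcome percentages are read from that list, so denominators may differ between arms for reasons other than prescribing

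*Protocol article*

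**What the plan says.** **The review.** The first limitation in the Discussion of the protocol article presents the introductory session as a data-quality measure: "getting the GPs to review their list of patients with diabetes (i.e., enter or remove patients"), with diagnostic codes put right. It adds that correctly registered patients then appear in the Diabetes Overview automatically.

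**Who gets it, and when.** The session is described under Intervention arm: "an introductory webinar (90 min in month 1) is held to learn GPs about how to use the electronic" platform. Table 1 counts it as part of what a practice in the intervention receives: "Each general practice will receive four conferences in 1 year each lasting approx. 45 min and one introductory webinar (90 min"). Under Comparison arm: "The control group will get the intervention after the primary intervention ends, that is, after month 12".

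**Where the outcomes come from.** Under Data collection: "Clinical outcomes will be collected from an IT-platform", namely the Diabetes Overview, as a screenshot of practice-level totals that a contact person e-mails to the project group. National registers for laboratory results, prescriptions and hospital contacts, among others, are obtained as well.

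**What is compared.** "The main analysis concerns the difference between the intervention and control group at month 12". The sentence that follows it names the Overview and the survey as the data analysed and does not mention the registers. The Discussion likewise identifies the Overview screenshots as the source of the primary and secondary patient outcomes. No baseline is taken from the control arm (Blinding; Data collection).

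**The concern.** Each clinical outcome is a percentage of listed patients who meet some condition. Editing the list changes the denominator, and sometimes the numerator, without any change in treatment. If one arm edits after randomisation, by GPs who know their allocation, and the other arm is not asked to, randomisation no longer guarantees that the two month-12 percentages refer to comparable patients. The article treats the review purely as a safeguard and does not remark that, under its own timetable, it reaches one arm before the primary time point.

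All three primary clinical outcomes are at stake. The within-arm analyses are affected too. In the intervention arm month 0 precedes the review and month 12 follows it. In the control arm, as the text reads, month 12 precedes it and month 24 follows it.

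**Working it through.** **Step 1: the chain of statements.**

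| Link | Place in the protocol article | Content |
|---|---|---|
| Review happens at the introductory session | Discussion | Patients added or removed, codes corrected |
| Session belongs to the intervention | Intervention arm; Table 1 | Month 1, 90 minutes |
| Controls get the intervention later | Comparison arm | After month 12 |
| Primary comparison | Difference between intervention and control group | Month 12, Overview data |
| List feeds the Overview | Discussion | Correct registration leads to automatic display |

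The Discussion calls the session a conference and the Intervention arm section calls it a webinar, but both mean the introductory session. Nothing in the text gives controls this session, or asks them for a list review, before month 12.

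**Step 2: the plan's own figures.** The Bonferroni threshold reproduces: 0.05/3 = 0.0167. The stated powers (0.8870, 0.9941, 0.9848) cannot be recomputed because their inputs are in Additional file 5, which is not shown. The article gives no figure for list errors.

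**Step 3: how far editing alone can move a percentage.** All inputs here are assumptions. Let p be the treated share before editing, r the number of edited patients as a fraction of the list, and q the treated share among them.

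- Removing: new rate = (p - r×q)/(1 - r)
- Adding: new rate = (p + r×q)/(1 + r)

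With p = 50% and r = 10%:

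| q | Removing | Shift (points) | Adding | Shift (points) |
|---|---|---|---|---|
| 0% | 0.500/0.9 = 55.6% | +5.6 | 0.500/1.1 = 45.5% | -4.5 |
| 25% | 0.475/0.9 = 52.8% | +2.8 | 0.525/1.1 = 47.7% | -2.3 |
| 50% | 0.450/0.9 = 50.0% | 0 | 0.550/1.1 = 50.0% | 0 |

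Over p = 30% to 70%, r = 5% to 15% and q from 0 to p, the shift runs from about -9.1 to +12.4 points. Both ends need p = 70%, r = 15% and every edited patient untreated, so they are extremes and not expectations.

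**Step 4: what a partial artefact would do to the test.** The planned effect in standard-error units is z(power) + z(1 - α/2). For outcome 1 with α = 0.05 this is 1.211 + 1.960 = 3.171. Suppose an artefact equals 25% of that, 0.793, and there is no true effect. At the 0.0167 threshold (critical value 2.394) the two-sided rejection rate is Φ(0.793 - 2.394) + Φ(-0.793 - 2.394) = 0.055. If the power was computed at α = 0.0167, it is 0.068. The corresponding ranges are about 0.10 to 0.12 for outcome 2 and 0.087 to 0.105 for outcome 3. The 25% is an assumption, and the calculation is a normal approximation.

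**Step 5: can the planned data correct it?** The screenshots carry no patient identifiers, so added or removed patients cannot be traced. Without a control baseline, list change cannot be compared between arms.

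**The case against.** - **The effect may be nil.** The article does not say how many patients are edited or how they are treated. Additions and removals pull in opposite directions when the edited patients are treated less than the rest, and there is no shift if they are treated at the same rate. This stands. A reader might infer that the denominators will differ, or that the intervention will look better than it is; the documents support neither.
- **Exposure is uneven.** The albuminuria and LDL subgroups are defined by laboratory findings, so outcomes 2 and 3 are exposed mainly through membership of the diabetes list. Outcome 1 is further exposed only if comorbidity codes are also revised, and the text does not say which codes are meant. This stands.
- **The one-arm reading is inferred.** The Discussion names no arm, the flow chart and schedule are not shown, and controls may tidy their lists unprompted. The order of the control arm's month-12 screenshot and its own introductory session is also not spelled out. But the sections on the two arms, read together, point one way.
- **Better identification is part of a pragmatic package.** The webinar "is held to learn GPs about how to use the electronic “Diabetes Overview” to identify and manage patients with T2D". Finding patients and then treating them is indeed an intended effect. Removing miscoded patients is measurement, and the Discussion itself justifies the review as data quality.
- **Registers are already planned.** They are, and the full protocol or analysis plan may give them a larger role. The article's description of the main analysis gives them none. Their availability makes the remedy cheaper but does not by itself remove the asymmetry.

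**Conclusion.** The point holds as a one-sided risk in outcome ascertainment. Followed as written, the plan asks unblinded intervention practices to edit the counted population after randomisation, asks nothing comparable of controls before month 12, and has no means within the Overview data of telling a list effect from a prescribing effect.

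Size and direction cannot be established from the documents. With 50% treated and 10% of the list edited, the shift lies between -4.5 and +5.6 points when edited patients are treated no more often than the rest, and it is zero when they are treated equally often. If they were treated more often than the rest, the signs would reverse.

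The stronger reading, that the month-12 comparison is biased by a known amount in favour of the intervention, is not supported. What is supported is that neither a positive nor a null result could be cleared of this explanation.

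**What to change.** 1. **Same review in both arms.** Have control practices carry out the identical list review immediately before their month-12 screenshot and before any conference content. Coming at the end of the comparison period, it cannot influence their earlier prescribing, so the aim of leaving controls undisturbed is kept. It also puts the control arm's month-12 and month-24 readings on the same footing. It does not repair the intervention arm's month-0 reading.
2. **Registers with one case definition.** Compute the medication and laboratory outcomes from the registers already listed, applied identically in both arms whatever the practice's own coding. Make this the primary source where the registers can identify the population, and otherwise a prespecified sensitivity analysis. The article does not show that they can identify every subgroup managed in general practice, so this needs checking first. Blood pressure is not evidently held in the registers named and would rest on step 1.
3. **Estimand.** If subgroups are dated at randomisation, state that the outcome becomes that of a baseline cohort and no longer the month-12 cross-section. This is a change of estimand and goes beyond wording.
4. **Limitations text.** State in the Discussion that, under the current plan, the list review reaches only the intervention arm before month 12.

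Cost: some control-practice time at month 12, register programming, and slower delivery than a screenshot.

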## Trial status

This trial was registered on ClinicalTrials.gov with study ID NCT05268081 on 4 March 2022. At the time of submission, recruitment to the trial, which started on 10 December 2021, is ongoing. The anticipated study completion date is September 2024. Protocol version number and date: 1.0, 4 March 2022.

## Data Availability

Restrictions apply to the availability of these datasets. Register data will be used under license for the current study. Survey data and patient outcomes data are not publicly available as per the written consent signed by general practitioners and endocrinologists. Data are, however, available for research purposes from the authors upon reasonable request and with permission from study participants.

## Abbreviations

T2D: Type 2 diabetes
GP(s): General practitioner(s)
